**Ethics and dissemination:**

The study has been approved by the Medical Ethics Review Committee of the Amsterdam UMC, location Academic Medical Centre, Amsterdam, the Netherlands. Study findings will be disseminated via presentations at conferences and publications in peer-reviewed journal.

**Trial registration number:**

The Netherlands Trial Registry, NL6953 (old: NTR28773).

Strengths and limitations of this studyThe main strength of this study is that it can accumulate data from large number of patients with long-term follow-up up to 11 years and that it captures all surveillance visits, long-term outcomes and mortality post-endovascular aneurysm repair.The sample size will be large enough to enable survival and regression analyses in sub-groups of patients.The main limitation of the study is due to the nature of retrospective data, it allows only the collection of data that was documented in the patient medical records.

## Introduction

Endovascular aneurysm repair (EVAR) of the abdominal aorta has become the primary treatment of patients with an abdominal aortic aneurysm (AAA).^1^ Both the Society for Vascular Surgery (SVS) International Guidelines and the instructions for use (IFU) of endograft manufacturers recommend yearly imaging surveillance for all patients after EVAR.^2^ However, if the patient is classified as ‘low risk’ for complications based on initial post-operative imaging, the 2019 European Society for Vascular Surgery (ESVS) guidelines recommend delaying imaging until 5 years after repair.^3^ This movement towards reducing the imaging frequency will benefit patients, medical centres and healthcare costs.

Imaging surveillance by CT angiography (CTA) may increase the attributable lifetime cancer risk of patients, as well as putting them at risk of developing nephropathy due to contrast exposure. If yearly CTA is replaced by duplex ultrasonography (DUS) patients still experience the burden of additional hospital visits. Moreover, compliance with yearly imaging is suboptimal and non-adherence to yearly imaging does not appear to be associated with poorer outcomes.^4 5^

It has been questioned whether yearly imaging is necessary for all EVAR patients, and if a specific group of patients can be identified for which surveillance intervals can safely be extended, as is suggested by the new guideline.^3^ For these reasons, in the Netherlands the Observing a Decade of Yearly Standardised Surveillance in EVAR patients with Ultrasound or CT Scan (ODYSSEUS) study has been designed. In this study of approximately 2000 patients with 6–11 years of follow-up, we aim to determine when, and in which patients, it is safe to deviate from the current annual surveillance protocols.

### Background and relevant literature and data

Before initiating the ODYSSEUS study, we conducted a survey among Dutch vascular surgeons to find out if they support the possibility of reducing the frequency of imaging surveillance. In this survey, vascular surgeons reported the main reasons patients did not comply with follow-up visits, that is, they had forgotten the appointment or were prevented by force majeure. Most physicians estimated that less than 10% of their patients had missed one or more follow-up visits post-EVAR. This might be an overestimation of the true adherence to follow-up visits, as these observations are in contrast with a study reporting that only 43% of patients had complete surveillance.^4^

We also asked participating vascular surgeons to upload their standard post-EVAR protocol to investigate if there were differences between centres in the Netherlands. In all centres, imaging took place within the first 3 months after surgery, mostly by CTA. Most centres comply with their own post-EVAR surveillance protocols which have many commonalities with the SVS and ESVS guidelines. Only one centre uses precisely the same post-EVAR surveillance protocol as recommended by the SVS guidelines. Another centre had already reduced follow-up imaging to once every 5 years, using either CTA or DUS as is stated in the new ESVS guidelines.^3^ While vascular surgeons still seem to adhere to their hospital-specific protocol, they do support the need for reducing follow-up by selecting a group of patients for which yearly follow-up can safely be omitted. However, some surgeons indicated that more evidence is needed than is available in the current literature.^6 7^

In studies that have investigated the indications for post-EVAR intervention, it is stated that 61%–98% of interventions were necessary because of symptoms and not because of findings at surveillance imaging. This suggests that post-EVAR surveillance protocols provide no benefit to a large group of patients, as complications occur in between surveillance visits.^8 9^ Imaging surveillance may even lead to unnecessary interventions and it does not appear to be associated with improved survival.^9 10^ We hypothesise that the requirement for routine imaging for patients at low risk can be reduced. However, novel endovascular devices still require more intensive surveillance as the short- and long-term results of those devices remain undetermined.

## Study objectives

The objective of this study is to evaluate whether imaging surveillance frequency might have been safely reduced in a selected group of EVAR patients, for example, in patients with an asymptomatic or symptomatic infrarenal AAA who underwent EVAR and who had no abnormalities on the 3-month postoperative CTA. The clinical course of a large cohort of patients will be evaluated with follow-up ranging between 6 and 11 years. Baseline patient characteristics, aortic anatomy and details of the operation will be derived from the patient’s medical record. The first milestone during follow-up is the first postoperative CTA. This scan either shows complications such as endoleaks, malposition or migration of the graft, or the absence thereof. All follow-up visits, imaging studies, as well as all interventions after EVAR and outcomes will be registered. Our hypothesis is that patients with less follow-up will have better outcomes regarding the number of interventions and aneurysm-related mortality compared to patients with annual follow-up. Regarding the intervention rates, it is expected that adherence to imaging surveillance may detect more abnormalities triggering re-interventions which in itself may cause additional complications and perhaps even a decrease in survival rates. We hypothesise that the need for routine imaging for patients with no abnormalities at their initial CTA can be decreased.

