### Primary and secondary endpoints

#### Main study endpoint

The number of patients with an intervention and aneurysm-related mortality classified for patients with and without yearly imaging surveillance.

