#### Secondary study endpoints

Date, type, indication and outcome of all postoperative imaging during follow-up.Type I, type II, type II and type IV endoleak, graft or outflow (iliac) occlusion, endograft infection detected by postoperative imaging, if present.Date and type of intervention during follow-up, if present.Date of aneurysm rupture during follow-up, if present.Date of death during follow-up, if present.Costs of all EVAR-related imaging and outpatient clinic visits.

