### Sample size and power

Sample size calculation for this study is based on an expected difference of 7% in the proportions of patients not requiring interventions after 7 years between patients undergoing yearly standardised imaging surveillance (75% intervention-free rate^18^) versus those s not undergoing standardised imaging surveillance(82% intervention-free rate^19^). To detect this difference with 90% power and a 0.05 significance level, 719 patients per group are required and 1438 in total. To correct for the fact that the first CTA of approximately 20% of patients is abnormal, 1798 patients (1438/0.8) are needed.^20 21^ In addition, we expect incomplete data in 10% of the patients which results in a total number of 1997 patients (1798/0.9). With this sample size, we can also detect a 3% difference in aneurysm-related mortality with statistical significance. We chose a one-sided significance level (non-inferiority) of 0.05 and for standard proportion a 95% non-aneurysm-related mortality and thus 5% freedom from aneurysm-related mortality after 7 years: 0.95. For equivalence limit difference, we chose an acceptable difference between groups of 3%, in which if differences in aneurysm-related mortality equals 3%, they are considered non-inferior. Test-expected proportion is then equal to the standard proportion 0.97. Thus, the expected difference is 0, calculated with a power of 80%. This results in 653 patients per group and 1306 patients in total. Since the first CTA of approximately 20% of patients is abnormal, 1632 patients (1306/0.8) are needed. In addition, we expect incomplete data in 10% of the patients which results in a minimum of, 1813 patients (1632/0.9) are needed in total.

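### The pooled intervention endpoint includes interventions that imaging itself prompts, so a lower count without yearly imaging cannot by itself show a better or safer outcome

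*Protocol article*

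**What the plan says.** Group A has a normal first postoperative CTA and yearly imaging, defined as a scan at least every 16 months. Group B has a normal first CTA and does not meet that definition.

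- **Endpoint.** The Main study endpoint is "The number of patients with an intervention and aneurysm-related mortality classified for patients with and without yearly imaging surveillance". Study procedures counts all EVAR-related interventions except those for access-site wound complications. Statistical methods analyses freedom from intervention as a single quantity, by Kaplan-Meier, log-rank test and Cox regression.
- **Direction.** Study objectives expects that "patients with less follow-up will have better outcomes regarding the number of interventions and aneurysm-related mortality".
- **Mechanism.** The same section says that "adherence to imaging surveillance may detect more abnormalities triggering re-interventions", and adds that such re-interventions may themselves do harm.
- **Trigger shares.** The background section reports from other studies that "61%–98% of interventions were necessary because of symptoms and not because of findings at surveillance imaging".
- **Effect size.** Sample size and power uses an "expected difference of 7% in the proportions of patients not requiring interventions after 7 years": a "75% intervention-free rate" with yearly imaging against an "82% intervention-free rate" without it.
- **Data.** Secondary study endpoints lists "Date, type, indication and outcome of all postoperative imaging during follow-up". For interventions it lists date and type, and no indication.

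**The concern.** Imaging frequency is the exposure, and imaging generates part of the outcome. Fewer scans mean fewer findings to act on, so the pooled count can fall in group B whether or not those patients fare better. The study asks whether imaging could have been reduced without harm. For that question, two explanations of a lower count matter and point in opposite directions: procedures that were never needed were avoided, or abnormalities that needed treatment went unseen. The pooled endpoint gives the same answer under both. It can also conceal a rise in symptom-driven interventions, if that rise is smaller than the number of surveillance-triggered interventions lost. A significant result would then be cited in support of less surveillance without bearing on its safety.

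**Working it through.** **Inputs.** Sample size and power: 75% and 82% intervention-free at 7 years (25% and 18% with an intervention), 0.05 significance level, 90% power, 719 per group. Background section: 61% to 98% of interventions symptom-driven.

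**1. The plan's own figure.** Two-sided, unpooled variance:

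n = (1.960 + 1.282)² × (0.75×0.25 + 0.82×0.18) / 0.07² = 10.507 × 0.3351 / 0.0049 = 718.6, so 719 per group. The stated figure is reproduced (the pooled-variance formula gives 722).

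**2. Surveillance-triggered part of group A's 25 points.** Points = 25 × (1 − s), where s is the symptom-driven share.

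- s = 61%: 25 × 0.39 = 9.75 points
- s = 98%: 25 × 0.02 = 0.5 points

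**3. Break-even with the planned gap.** 7 / 25 = 28% surveillance-triggered, so s = 72%. This lies inside the 61% to 98% range. At s = 61%, losing 7 / 9.75 = 72% of the triggered interventions would be enough.

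**4. Chance of a significant result in B's favour from this mechanism alone.** Suppose every surveillance-triggered intervention disappears in B and the symptom-driven rate is the same in both groups, so that B has 25 × s. With 719 per group, power = Φ[(d − 1.96 × SE₀) / SE₁], where d is the gap, SE₀ uses the pooled proportion and SE₁ the separate ones.

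| Symptom-driven share | B with an intervention | Gap (points) | Chance of significance |
|---|---|---|---|
| 61% | 15.25% | 9.75 | 99.6% |
| 72% | 18.0% | 7.0 | 90% |
| 79.5% (mid-range) | 19.9% | 5.1 | 64% |
| 90% | 22.5% | 2.5 | 20% |
| 98% | 24.5% | 0.5 | about 4% |

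**5. A rise can sit inside a significant result.** At s = 61%, A is 25 × 0.61 = 15.25 symptom-driven plus 9.75 surveillance-triggered, which is 25%. Suppose B has 18 symptom-driven and none surveillance-triggered. The comparison is then exactly the planned 25% v 18%, with 90% power to favour B, although symptom-driven interventions are 18 − 15.25 = 2.75 points higher (18 / 15.25 = 1.18, a relative rise of 18%). B's split here is an illustration and not a figure from the article.

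**The case against.** The strongest reply is that the mechanism is the study's stated rationale and not an oversight. The background section says that surveillance may lead to unnecessary interventions. If symptom-driven interventions are equal in both groups and B is spared 7 points of procedures, that is a real gain for patients. This stands. A reader might infer that such a result would benefit nobody, and the article does not support that. But whether the avoided procedures were unnecessary is a hypothesis, and the pooled count assumes it without testing it.

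Second, safety is not ignored. Aneurysm-related mortality is also a primary outcome, with a 3% non-inferiority margin and its own sample size (653 per group). Rupture is a secondary endpoint with a planned log-rank comparison. The Discussion words the hypothesis jointly, as fewer interventions with no difference in aneurysm-related mortality. It would therefore be wrong to infer that the plan tests interventions alone. What remains uncovered is the symptomatic intervention that the patient survives without rupture.

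Third, a reader might infer that B is bound to have fewer surveillance-triggered interventions, or that the planned gap is an artefact. Neither follows. B is still imaged, only less regularly, and its scans can prompt interventions. Above a 72% symptom-driven share, which is 26 of the 37 points in the quoted range, the mechanism cannot produce the whole gap. At 98% it yields 0.5 of the 7 points.

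Fourth, an extra analysis by trigger could be left to a fuller plan. That is fair for the analysis detail. The point here concerns the reading that Study objectives does fix: fewer interventions as a better outcome.

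**Conclusion.** The concern holds as a limit on interpretation. A lower pooled intervention count in group B cannot by itself show a better outcome or that imaging could safely have been reduced. Surveillance-triggered interventions account for 0.5 to 9.75 of group A's 25 points. They could explain the whole planned 7-point gap at a symptom-driven share of 72% or less, and part of it above that.

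These figures rest on three assumptions that the article cannot confirm: that the 61% to 98% range, taken from other studies, applies to first interventions in patients with a normal first CTA; that every intervention not driven by symptoms is surveillance-triggered; and that all of these disappear in B. For the chances of significance, the symptom-driven rate is also held equal in both groups. If B keeps some triggered interventions, the contribution is smaller in proportion. The sample size calculation itself is correct.

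**What to change.** Keep any intervention as the endpoint, and add the following.

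- Classify each first intervention as surveillance-triggered, symptom- or rupture-driven, or undetermined, using the indication and outcome of the preceding imaging together with the medical record.
- Compare symptom-driven interventions between A and B by cumulative incidence and by cause-specific hazards.
- Reword Study objectives so that fewer total interventions is read as favourable only together with symptom-driven interventions, rupture and aneurysm-related mortality. This also brings it closer to the joint wording in the Discussion.

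The cost is the work of linking each intervention to the scan before it. Some misclassification is unavoidable, because indication is a listed field for imaging but not for interventions, and some cases will have no preceding scan to link. The symptom-driven analysis has fewer events, so its intervals will be wider. The planned sample size need not change.

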## Methods and analysis

The study protocol has been designed according to the Standard Protocol Items: Recommendations for Interventional Trials statement and the CONsolidated Standards of Reporting Trials.^11 12^

### General study design

A multicentre retrospective cohort study in 17 medical centres in the Netherlands. Data will be collected from the medical records of all consecutive patients with AAA who underwent EVAR between January 2007 and January 2012. This selection provides a theoretical length of follow-up of 6–11 years on December 2018. Patients will be divided into three groups: (A) patients without abnormalities at their first postoperative CTA with yearly imaging surveillance, (B) patients without abnormalities at their first postoperative CTA without yearly imaging surveillance and (C) patients with abnormalities at their first postoperative CTA (figure 1). This retrospective design has the advantage of collecting long term follow-up data. The Dutch Dream trial found that the number of interventions starts to rise 4 years after EVAR and the long-term results of the EVAR-1 trial show that EVAR has an early survival benefit but inferior late survival compared to open surgical repair.^13 14^ This is in contrast to the recently published long-term results of the OVER trial in which no difference was observed between EVAR and OSR in the primary outcome of all-cause mortality.^15^ Hence, a prospective study would take approximately 8 to 10 years to gather enough patients with adequate follow-up.

**Figure 1 F1:**
[figure not shown]
Patient subgroups. AAA, abdominal aortic aneurysm; CTA, CT angiography; EVAR, endovascular aneurysm repair.

The standard of care is defined by the current guidelines and IFU. The usual follow-up schedule in the IFU is: CTA and abdominal X-ray at 30 days, 6 and 12 months and yearly thereafter. The 2019 ESVS guidelines recommend a CTA 30 days after EVAR. If there is adequate seal and no endoleak, patients are classified as low risk and CTA follow-up may take place 5 years later. If there is an inadequate seal and endoleak type I/III patients could be either evaluated for re-intervention or if sac shrinkage occurs yearly DUS is recommended. In the 2018 SVS guideline, CTA at 1 and 12 months is recommended and if neither endoleak nor sac enlargement is documented, DUS is suggested for annual postoperative surveillance. In our study design, the definition of compliance is undergoing imaging surveillance every 16 months since patients in most centres will be rescheduled if they missed their annual follow-up visit. Device-specific complications after EVAR will also be examined.

### Study population

Patients eligible for this retrospective study are all adults who underwent elective EVAR for asymptomatic or symptomatic infrarenal AAA between January 2007 and January 2012. Table 1 gives a more detailed overview of the inclusion and exclusion criteria.

**Table 1 T1:** Retrospective cohort

Inclusion criteria	Exclusion criteria
Age ≥18 years	Connective tissue disease
Patient with an (a)symptomatic infrarenal abdominal aortic aneurysm EVAR between January 2007 and January 2012	Patients who objected to their retrospective data being used
Patients with an initial postoperative CTA within 90 days after EVAR	

CTA, computed tomography angiography; EVAR, endovascular aneurysm repair.

### Patient and public involvement

No patients were involved in the research design and conception of this research study.

### Date range of the study

Data will be extracted from patient medical records retrospectively and entered into a database with data validation from December 2018 until June 2020. At first, two researchers will extract data together to standardise data extraction. Next, to further improve the validity of the data two researchers will independently extract data and enter it into the secured data base. Disagreements will be noted and resolved by discussion and if necessary by asking another co-author to act as an arbiter.

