### Study procedures

The primary outcomes of this study are interventions and aneurysm-related mortality for patients who had a normal initial postoperative CTA and who do adhere to our definition of yearly imaging surveillance over a 6-year to 11-year follow-up period, compared to those who do not adhere to our definition.

Interventions are EVAR-related interventions defined by the SVS reporting standards as postoperative adjunctive manoeuvres.^16 17^ Interventions for wound complications at the access site are not included, since these are detectable without the use of imaging.

Date of death during follow-up, if applicable, will be obtained from patient medical records and verified by the Dutch municipal personal records database (GBA).

Details of all surveillance imaging are obtained from patient medical records and radiology reports. The time between imaging appointments is calculated to determine whether patients adhere to this studies definition of with yearly imaging surveillance, that is, within every 16 months.

Date, type, indication and outcome of all postoperative imaging during follow-up are obtained from patient medical records, specifically imaging order forms and radiology reports. A normal initial postoperative CT scan is defined as a CT scan which shows no endoleaks, endograft migration (>10 mm), kinking or obstruction. All imaging outcomes are based on the report compiled by radiologists. These reports will not be re-evaluated by an independent radiologist, since we want to base our outcomes on real life data.

Secondary outcomes are all-cause mortality, type I, type II, type III and type IV endoleak, graft or outflow (iliac) occlusion, aneurysm rupture and endograft infection. This is also obtained from patient medical records, specifically radiology reports and Dutch municipal personal records database (GBA).

Date of aneurysm rupture is obtained from patient medical records, specifically operative reports, radiology reports and progress notes.

Costs of all EVAR-related imaging and outpatient clinic visits will be calculated per patient. Cost is defined as volume times price. Prices from the ‘Cost manual of the Dutch Health Care Institute’’ will be used. Costs for the patients will also be included. The quality-adjusted life years, a generic measure of disease burden including both the quality and quantity of life, cannot be calculated with this retrospective design.

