Our study is subject to limitations due to the nature of administrative data and its retrospective and observational design. As with all studies using administrative data, it allows only the collection of data that was documented in patient medical records. It is also possible that some patients may have transferred to alternative surveillance protocols in different medical centres without our knowledge. The study will assess results in 17 medical centres over 11 years, during which time improvements in endograft and in clinical practice has occurred. Attrition bias due to loss to follow-up represents a threat to the internal validity of our cohort study. The mentioned e-survey has only been sent to participating vascular surgeons, perhaps surgeons participating in the ODYSSEUS study strongly believe that imaging surveillance frequency can be reduced. This may have provided a biased view of post-EVAR follow-up in the Netherlands. However, most of the high-volume EVAR centres in the Netherlands have been included. Another limitation is that no information is retrieved from patients’ medical records about when not to intervene and what the reason was for this decision.

In conclusion, with the ODYSSEUS study we aim to confirm the follow-up protocol of the recent ESVS guideline delaying imaging after 5 years if classified in the low risk group and therefore aim to investigate the intervention-free-survival and aneurysm-related mortality for patients with and without yearly imaging surveillance.

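### Double extraction does not keep the attribution of aneurysm-related death apart from the imaging dates that define the surveillance group, so differential misclassification of a primary endpoint is possible

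*Protocol article*

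**What the plan says.** Extraction is described in the protocol article under Date range of the study. Two researchers first work together to standardise their approach. After that, "two researchers will independently extract data and enter it into the secured data base". Disagreements are noted and "resolved by discussion and if necessary by asking another co-author to act as an arbiter".

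The exposure is built from the same records. Under Study procedures, "The time between imaging appointments is calculated to determine whether patients adhere to this studies definition" of yearly surveillance, meaning imaging at least every 16 months. Patients with a normal first CTA fall into group A or B on that basis (General study design).

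Aneurysm-related mortality is a primary endpoint (Main study endpoint). Study procedures gives a source for the date of death, namely the medical record verified in the municipal registry. It gives no source, definition or assessor for whether a death was aneurysm-related. Sample size and power plans this endpoint as a non-inferiority comparison with a 3-point margin. Study objectives states the expectation that less follow-up goes with better outcomes, including for aneurysm-related mortality.

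The first CTA is handled differently: "All imaging outcomes are based on the report compiled by radiologists", against a listed definition of a normal scan.

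**The concern.** Double extraction guards against slips and individual idiosyncrasy. It does not guard against an expectation shared by both extractors and by a co-author arbiter. In this study the imaging history is the exposure, so anyone working through the record to attribute a death can see which surveillance pattern the patient followed. Nothing in the described process puts the attribution before the imaging dates or conceals them from the arbiter.

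Deciding whether a death was aneurysm-related is a judgement, often from incomplete notes, and the expected event rate is low (about 5%). In a non-inferiority comparison, under-calling deaths in the less-imaged group moves the result towards the conclusion the study hopes to reach. A handful of deaths classified differently by group could affect whether the 3-point margin is met.

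**Working it through.** **Inputs from the article (Sample size and power).** Non-inferiority margin 0.03; one-sided alpha 0.05; power 80%; expected difference 0; standard proportion 0.95; 653 per group for this endpoint; 719 per group for the intervention endpoint.

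**Reproducing the plan's figure.** n = (1.645 + 0.842)² × 2 × 0.95 × 0.05 / 0.03² = 653 per group, which matches. The same paragraph also mentions 0.97, but that value would give 400, so the stated size rests on 0.95, that is, 5% aneurysm-related mortality.

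**Assumptions that are not in the documents.** True aneurysm-related mortality is 5% in group A and 8% in group B, exactly at the margin, so a correct test should declare non-inferiority 5% of the time. A share of aneurysm-related deaths is then called unrelated.

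**Formula.** With observed proportions pA and pB:

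- SE = √{[pA(1 − pA) + pB(1 − pB)] / n}
- False non-inferiority rate = Φ[(0.03 − (pB − pA)) / SE − 1.645]

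**Worked case: 10% under-called in group B only, n = 653.** pB = 0.08 × 0.90 = 0.072. SE = √[(0.0475 + 0.0668) / 653] = 0.01323. (0.03 − 0.022) / 0.01323 = 0.605. Φ(0.605 − 1.645) = Φ(−1.040) = 14.9%.

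**Worked case: 10% under-called in both groups, n = 653.** pA = 0.045 and pB = 0.072. SE = √[(0.0430 + 0.0668) / 653] = 0.01297. (0.03 − 0.027) / 0.01297 = 0.231. Φ(0.231 − 1.645) = Φ(−1.414) = 7.9%.

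| Share of deaths under-called | Group B only, n = 653 | Group B only, n = 719 | Both groups, n = 653 |
|---|---|---|---|
| 0% | 5.0% | 5.0% | 5.0% |
| 5% | 8.9% | 9.1% | – |
| 10% | 14.9% | 15.6% | 7.9% |
| 20% | 34.6% | 36.9% | 12.4% |

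**In deaths.** 653 × 0.08 = 52 aneurysm-related deaths in group B, so 10% is about 5 deaths. At 719 per group, 719 × 0.08 = 58, so 10% is about 6.

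Equal under-calling raises the rate a little, because it shrinks the absolute difference (from 0.030 to 0.027 at 10%). Most of the effect comes from error that differs between the groups, which is the kind that masking reduces.

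**The case against.** The strongest reply is that the article is a condensed account and is silent on masking, on the order in which forms are completed, and on who attributes cause of death. Such detail may sit in a full protocol. That stands as a limit: that the extractors make the attribution is an inference, drawn because the article describes nobody else. But the article does set out the extraction process, including standardisation and arbitration, and nothing in what it sets out separates outcome from exposure.

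Three stronger readings are tempting, and the documents do not support them.

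- A reader might infer that the researchers themselves judge whether the first CTA was normal. They do not. Findings come from radiologists' reports, and "These reports will not be re-evaluated by an independent radiologist, since we want to base our outcomes on real life data". The definition is a list: "A normal initial postoperative CT scan is defined as a CT scan which shows no endoleaks, endograft migration (>10 mm), kinking or obstruction". What remains is the abstraction of unclear report wording, which is a minor matter.
- A reader might take the remark in the Discussion that "perhaps surgeons participating in the ODYSSEUS study strongly believe that imaging surveillance frequency can be reduced" as evidence of bias among the extractors. That sentence concerns who was sent the e-survey, and nothing says that the extractors are those surgeons. The stated hypothesis is the relevant evidence of direction.
- A reader might conclude that the process will produce a false non-inferiority result. The documents show only that it could. The 10% and 20% shares are assumed, the one-sided error is a chosen scenario, and the truth is placed exactly at the margin. Two independent extractors would also have to err in the same direction.

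A practical objection also stands. Outcomes cannot be locked before any radiology is opened, because Study procedures names radiology reports as a source for rupture. The order proposed below allows for this.

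**Conclusion.** The concern holds in a limited form. The described double extraction with a co-author arbiter limits individual error, but it leaves attribution of aneurysm-related death unseparated from the imaging dates that define group A or B. Differential misclassification towards the stated hypothesis is therefore possible on a primary non-inferiority endpoint.

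As an illustration, under-calling 10% of aneurysm-related deaths in group B alone, about 5 or 6 deaths, would triple the false non-inferiority rate from 5% to about 15% at 653 per group (about 16% at 719). Equal under-calling in both groups gives about 8%. These figures assume a true 5% against 8% and the comparison of proportions used for the sample size. They are not estimates, since the documents give no misclassification rate. The change should be made because it is cheap and protects a judgement-dependent endpoint; the sample size is unaffected.

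**What to change.** Amend the extraction description under Date range of the study so that the same two researchers work in a fixed order, locking each form before the next is opened:

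1. Abstract and lock first-CTA status from the radiologist's report before any later record is entered.
2. Classify and lock each death as aneurysm-related yes, no or undetermined, and each rupture and intervention, from the records of that event. These include its operative and diagnostic radiology reports, as Study procedures requires. Do this before surveillance imaging dates are entered.
3. Enter surveillance dates last, and derive group A or B by program with the 16-month rule.

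Send disputed deaths to the existing arbiter as a summary without surveillance dates or group.

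The change reorders and locks existing forms. It needs no extra staff and no re-reading of scans. Extraction will be slightly slower, and masking will be incomplete where notes mention scans.
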